1. The iMBCT-I will improve sleep quality, level of mindfulness, quality of life and attitudes towards traditional psychotherapy and online psychotherapy by the end of the intervention (week 8).2. The iMBCT-I will decrease dysfunctional beliefs about sleep, anxiety and depression by the end of the intervention (week 8).3. The effect of the iMBCT-I will be maintained at the scheduled follow-up assessment (week 20).4. Mindfulness levels, attitudes towards traditional psychotherapy or online psychotherapy at baseline will have an influence on both the short-term (week 8) and long-term (week 20) effects of the iMBCT-I.

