### Sample size

With reference to the results of a large-scale randomized controlled trial conducted by Lee M. R. which compared the effects of online CBT-I with SHE on chronic insomnia patients, we estimated that the ISI score reductions in the iMBCT-I group and the SHE group were 7.7 and 3.1, respectively, with a common standard deviation of 5.5 (42). Assuming an alpha level of 0.05 and a power level at 0.9, the calculated minimum sample size was 30 participants per group. Estimating a dropout rate of 20%, we plan to recruit 80 participants in total.

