## Data collection and management

Assessments will be conducted at week 0 (baseline), week 8 (post-intervention) and week 20 (3 months after intervention). Details are displayed in **Table 1**.

**Table 1 T1:** Assessment schedule.

Outcome	Measure	Time of assessment			
		Screen	Baseline (week 0)	Post-intervention (week 8)	Follow-up (week 20)
Socio-demographics	SR	X			
CID	MINI	X			
Insomnia severity	ISI	X	X	X	X
Sleep quality	PSQI		X	X	X
Mindfulness level	FFMQ		X	X	X
Depression	PHQ-9		X	X	X
Anxiety	GAD-7		X	X	X
Quality of life	SF-12	X	X	X	X
Attitudes	ATSPPH-SF	X	X	X	X
Dysfunctional beliefs	DBAS-16		X	X	X
Sleep parameters	Actigraphy		X	X	X
Treatment adherence	Number of completed sessions			X	X

SR-self reported measure; MINI- Mini International Neuropsychiatric Interview (MINI) provided by two psychiatrists; ISI- Insomnia Severity Index; PSQI- Pittsburgh Sleep Quality Index; FFMQ- The Five Facet Mindfulness Questionnaire; PHQ-9- The Patient Health Questionnaire-9; GAD-7- The Generalized Anxiety Disorder 7-item scale; SF-12- The 12-item Short Form Health Survey; ATSPPH-SF- The Attitudes Toward Seeking Professional Psychological Help Scale-Short Form; DBAS-16- Dysfunctional Beliefs and Attitudes about Sleep Scale 16-item version.

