#### Secondary outcome analysis

Changes between groups in scores of PSQI, FFMQ, PHQ-9, GAD-7, SF-12, ATSPPH-SF and DBAS-16, insomnia remission rate and all sleep parameters values from baseline to week 8 will be evaluated using paired t-tests (for normally distributed data)/Mann-Whitney U tests (for non-normally distributed data). Mixed-effect models for repeated measures will be used to evaluate the effects of the online MBCT-I on scores of ISI, PSQI, FFMQ, PHQ-9, GAD-7, SF-12, ATSPPH-SF and DBAS-16 as well as all sleep parameters values over time (from baseline to week 20). The model will include treatment group, time, treatment-by-time interaction and baseline covariates.

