#### Exploratory analysis

In order to identify predictors of effectiveness, subgroup analyses will be conducted to compare the efficacy of iMBCT-I among participants with different characteristics, such as demographics, mindfulness levels (FFMQ) and attitudes towards psychotherapy (ATSPPH-SF). Additionally, the relationship between the number of attended sessions and treatment efficacy will be explored using regression analysis, with session attendance as an independent variable and ISI score reduction as the dependent variable.

Structural equation models will be applied to identify possible mediators and moderators of intervention efficacy such as mindfulness levels (FFMQ) and attitudes towards psychotherapy (ATSPPH-SF) at baseline.

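### Baseline mindfulness and attitudes are listed as possible mediators, a role they cannot play, and no arm-by-baseline interaction is written for the moderation question in secondary hypothesis 4

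*Protocol article*

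**What the plan says.** Four places in the protocol article bear on this.

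- **Introduction, secondary hypothesis 4.** Mindfulness and attitudes towards traditional or online psychotherapy "at baseline will have an influence on both the short-term (week 8) and long-term (week 20) effects of the iMBCT-I". This is a statement about effect modification.
- **Exploratory analysis, subgroups.** To find predictors of effectiveness, "subgroup analyses will be conducted to compare the efficacy of iMBCT-I among participants with different characteristics", with FFMQ and ATSPPH-SF among the examples.
- **Exploratory analysis, structural equation models.** The models look for "mediators and moderators of intervention efficacy such as mindfulness levels (FFMQ) and attitudes towards psychotherapy (ATSPPH-SF) at baseline".
- **Secondary outcome analysis.** For the repeated-measures model, "The model will include treatment group, time, treatment-by-time interaction and baseline covariates". No other interaction is written anywhere.

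Table 1 schedules FFMQ and ATSPPH-SF at baseline, week 8 and week 20, so post-baseline values will exist. The Exploratory analysis section does not name them, or change in them, as mediators. The Discussion says that the exploratory work will help to identify who is better suited to iMBCT-I and to guide treatment choice.

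**The concern.** A mediator lies on the path from treatment to outcome, so treatment must be able to move it. A score taken before randomisation cannot be moved by treatment. An analysis of mediation through baseline FFMQ or baseline ATSPPH-SF therefore has a known expected answer, zero, whatever the true mechanism. A null result could be misread as evidence that mindfulness does not carry the effect. A non-null result would be chance imbalance between arms.

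A baseline score can be a moderator, and hypothesis 4 asks about exactly that. Moderation is a difference in the between-arm contrast across values of the baseline score, so it needs both arms and an arm-by-score term. The text does not write one. If the subgroup sentence were carried out within the iMBCT-I arm only, a factor that predicts improvement in everyone would look like a predictor of benefit from iMBCT-I. That matters because the Discussion offers these results as help in choosing treatment.

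**Working it through.** The plan gives no figure for these analyses. The inputs come from Sample size: ISI reductions in the "iMBCT-I group and the SHE group were 7.7 and 3.1, respectively, with a common standard deviation of 5.5", two-sided alpha 0.05, power 0.90, 30 per group, 20% dropout, 80 in total.

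**1. The plan's own figure.** Effect = 7.7 − 3.1 = 4.6 points. n per group = 2 × (1.960 + 1.282)² × 5.5² / 4.6² = 2 × 10.51 × 30.25 / 21.16 = 30.04. This matches the stated 30 (31 if rounded up, 32 with the noncentral t). Allowing for dropout, 32 / 0.8 = 40 per arm, or 80 in total. The inputs are therefore read correctly.

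**2. Mediation through a baseline score.** Indirect effect = a × b, where a is the between-arm difference in the mediator and b is its association with outcome given arm. Randomisation makes the expected value of a zero for any baseline score, so a × b is zero in expectation however large b is. In one trial of 40 per arm, a varies around zero with standard error √(4/80) = 0.22 SD of the score. If the score correlated 0.4 with ISI reduction (an assumption; b = 0.4 × 5.5 = 2.2), that is 0.22 × 2.2 ≈ 0.5 ISI points of apparent mediation produced by imbalance alone. In 5,000 simulated trials of 64 participants, the mean indirect effect was 0.00 at correlations of 0.3, 0.4 and 0.5.

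**3. Within-arm comparison against interaction test.** The same simulation had no true moderation: reduction = 3.1 + 4.6 × arm + b × score + error, total SD 5.5, b equal in both arms. The correlations are assumed; the protocol gives none. Share of trials in which the score is declared a predictor at p < 0.05:

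| Correlation (assumed) | iMBCT-I arm only, median split | iMBCT-I arm only, regression | Arm × score, both arms |
|---|---|---|---|
| 0.3 | 27% | 39% | 5% |
| 0.4 | 44% | 63% | 5% |
| 0.5 | 64% | 85% | 5% |

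The first two columns apply only if the comparison is made within the arm. The median split is an illustration; the protocol does not specify one.

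**4. Precision of the correct test.** For a 50:50 split, SE of the interaction = 5.5 × √(16/N); for a continuous score, per SD, 5.5 × √(4/N). Detectable differences use the noncentral t with N − 4 degrees of freedom. N = 80 is the full ITT set with LOCF; N = 60 is 30 completers per group.

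| | N = 80 | N = 60 |
|---|---|---|
| SE, 50:50 split | 2.46 | 2.84 |
| Detectable with 80% power, split | 7.0 points | 8.1 points |
| Power for a 4.6-point interaction, split | 46% | 36% |
| SE per SD, continuous | 1.23 | 1.42 |
| Detectable with 80% power, per SD | 3.5 points | 4.1 points |

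With a split, only an interaction well above the assumed 4.6-point treatment effect would be found reliably.

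**5. Time order.** With assessments at weeks 0, 8 and 20 only, change in FFMQ to week 8 precedes the week-20 ISI but coincides with the week-8 ISI. The week-20 outcome is the only one with a mediator measured before it.

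**The case against.** The strongest reply is that the sentence names moderators as well as mediators. A baseline score is a proper moderator, and a moderation term in the planned structural equation model would test hypothesis 4. The baseline restriction may have been meant for moderators only. Primary outcome analysis defines the effect of MBCT-I as the coefficient for MBCT-I against SHE, so comparing efficacy across subgroups can fairly mean comparing that contrast. Interaction terms and model paths are commonly left to the analysis plan, which the article says exists. The section is headed exploratory, and so is the whole trial under Trial design.

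Most of this stands. A reader might infer that neither the subgroup analyses nor the structural equation models can answer hypothesis 4, or that the plan will report prognostic factors as treatment predictors. The documents do not support that: both analyses can answer the hypothesis if they compare the randomised difference with an interaction test, and the within-arm reading is possible but not established. Nor does the protocol propose a median split or a mediation model with mediator and outcome both at week 8. Low power would affect any interaction test at this size, so it is no evidence that the wrong test was chosen.

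The reply does not remove the mediator wording. That is a stated rule, not an omitted detail: as printed, one list and one time point cover both roles. The exploratory heading also sits beside a numbered secondary hypothesis and a statement about guiding treatment choice.

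**Conclusion.** The point holds for the mediator wording without further assumption: baseline FFMQ and baseline ATSPPH-SF cannot mediate a randomised treatment, and the expected indirect effect is zero. For moderation the finding is narrower. Hypothesis 4 is not tied to a written arm-by-baseline interaction, and the subgroup sentence is loose enough to allow a within-arm comparison. If it were read that way, false predictors would appear in 27% to 85% of trials under assumed prognostic correlations of 0.3 to 0.5, against about 5% for the interaction test. If it is read as a between-arm comparison, that error does not arise.

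Even the correct test is imprecise. With SD 5.5 and a 50:50 split, it detects 7.0 to 8.1 ISI points with 80% power for N = 80 to 60. The primary analysis is unaffected; the stake is what may be claimed about mechanism and about who benefits.

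**What to change.** 1. In Exploratory analysis, apply the baseline restriction to moderators only.
2. Name the test of hypothesis 4: arm × continuous baseline FFMQ and arm × continuous baseline ATSPPH-SF (both versions of the scale, since the hypothesis covers traditional and online psychotherapy), in all randomised participants, for ISI at weeks 8 and 20, each interaction reported with its 95% CI. State that subgroup displays compare the iMBCT-I minus SHE difference.
3. Define mediators as change from baseline to week 8 in FFMQ and ATSPPH-SF, with week-20 ISI as the outcome, adjusted for the baseline value of the mediator and baseline ISI. The mediator is not randomised, so add a sensitivity analysis for unmeasured confounding.
4. Do not adjust for week-8 ISI by default. It is affected by treatment and measured at the same time as the mediator, so conditioning on it can remove part of the effect sought. Use it at most in a sensitivity analysis with its assumptions stated.
5. Label both analyses, and the Discussion statement on guiding treatment choice, as hypothesis-generating.

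The cost is wording only; every measurement is already in Table 1. The drawback is wide intervals, which the report should show.

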### Plans to give access to the full protocol, participant level-data and statistical code

The full protocol and statistical analysis plan are available on request to the corresponding author after the manuscript published according to the data dissemination guidelines.

## Oversight and monitoring

### Composition of the coordinating center and trial steering committee

This is a single-center study designed and implemented by the Tongji Hospital, School of Medicine, Tongji University. The steering committee is comprised of authors [name] and [name]. The committee members participated in the study design and provided suggestions for the experiment. The data security monitoring committee is independent of the host organization, including statistician and [name] as the chairman. The supervision and management department can conduct audits to assess the clinical research behavior and compliance with the protocol, SOPs, GCP, and applicable regulatory requirements.

### Composition of the data monitoring committee, its role and reporting structure

This study do not have Data Security Monitoring Board (DSMB) because no serious adverse events were reported with MBCT-I in previous studies. Research physicians will be contacted as security officers within 24 h if an adverse event occurs. If the safety officer assesses that the adverse event is related to the intervention, relevant safety measures will be taken. Serious adverse events will be reported to Tongji Hospital of Tongji University Institutional Review Board.

### Adverse event reporting and harms

All adverse events reported by participants and observed by researchers, as well as causal assessments of adverse events following the intervention, will be recorded in the Case Report Form (CRF). MBCT-I is classified as a non-pharmacological treatment. To date, few instances have been identified that could potentially harm participants’ health (67, 68). The sleep restriction component (which involves reducing the time spent awake in bed to enhance sleep efficiency) may initially cause discomfort for participants. Other potential adverse reactions may include distress, anxiety, or exacerbation of insomnia during the psychotherapy process. All adverse events occurring during the study will be carefully monitored and documented to determine their relationship to the intervention.

### Frequency and plans for auditing trial conduct

The study will be supervised by the hospital safety supervision committee, which will look after the study design re-evaluation, procedure execution, medical ethics, participant safety, and data management. The research team will discuss protocol amendments and notify the PI. The PI will have a copy of the modified agreement. Any behavior deviating from the agreement will be recorded with the reporting form.

### Dissemination plans

The results of this study will be communicated in international conferences and be published in peer-reviewed journals. Both positive and negative results will be reported.

## Discussion

To the best of our knowledge, this study protocol is the first to investigate the feasibility and effectiveness of therapist-guided iMBCT-I compared with sleep hygiene education in patients with chronic insomnia disorders via a randomized controlled design. This study will also test the effectiveness of iMBCT-I on secondary outcomes such as the level of mindfulness, quality of life, symptoms of depression and anxiety, and dysfunctional beliefs about sleep. We anticipate that iMBCT-I will reduce insomnia severity and that this effect will be maintained at the follow-up assessment. We also anticipate improvements in the level of mindfulness, quality of life, symptoms of depression and anxiety and dysfunctional beliefs about sleep, as they are closely correlated with sleep quality (68–71). We believe that this study could fill the research gap in evidence regarding the effectiveness of MBCT for CID. We will provide a more cost-effective, accessible and lower-intensity online intervention.

This study protocol has some strengths. First, the intervention is innovative, integrating the benefits of both mindfulness and CBT-I while being delivered by trained therapists. The iMBCT-I program has been tailored to the Chinese context and adapted into more manageable 1.5-hour sessions to enhance participant compliance and engagement. Second, we will conduct a comprehensive assessment of participants’ sleep, utilizing both subjective (questionnaire, sleep diary) and objective (actigraphy) measures in many different dimensions (insomnia severity, sleep quality, sleep parameters, sleep states and sleep-related dysfunctional beliefs). All measurement tools in this study are used worldwide, with proven reliability and validity. In addition, exploratory analysis of factors influencing outcomes will provide insights into identifying subgroups of individuals who are better suited for receiving iMBCT-I, which will aid in guiding treatment choices for clinical practitioners and patients with CID.

This study protocol has several limitations. First, a double-blinded study design cannot be used in the current study. Another limitation is the structural difference between the intervention and control groups in terms of treatment duration and provider contact. While the iMBCT-I group undergoes an 8-week structured program with therapist-led sessions, the SHE group receives only a single-session educational intervention. This discrepancy may introduce non-specific effects, as greater provider interaction and prolonged engagement in the intervention group might contribute to improvements in sleep beyond the specific effects of MBCT-I. Future studies will consider using structurally equivalent iCBT-I and provider contact as a comparator to investigate whether iMBCT-I demonstrates superior efficacy.
